### Data management/Data cleaning (phase I-IV)

Data quality scripts for phase I, II, IV will be written in STATA. Data quality checks for phases I, II, and IV (quantitative data) will be done through RedCap (a secure web platform for building and managing research databases). Since TIER.Net will be used as the primary data source for phase I data extraction in the city of Johannesburg region F, where there are data quality issues, the study team will liaise with the facility staff and developmental partners in the region to assist with data clean-up activities. Data quality issues with the ITREMA data (phase II) will be communicated to the ITREMA study quality assurance officer for rectifying. Data quality checks for phase III (qualitative data) will be done in Microsoft Word (before exporting data to NVIVO). All transcripts will be checked for completeness and accuracy against original interviews. Creditability of data analysis will be ensured through triangulation of data sources (i.e., original interviews, field notes, transcripts, medical record).

### Data storage and access (phase I-IV)

Data will be captured and stored electronically, and password protected in the Microsoft Word, Microsoft Excel format and/or RedCap and will only be accessible to an investigator and supervisors only. RedCap access is restricted to only those users who are registered on the system. All data from RedCap, Microsoft Word, Microsoft Excel, STATA, and voice files will be stored in access restricted folders on the Ezintsha server which will only be accessible to an investigator and supervisors. Any paper versions of data will be discarded after use. Data storage and access measures will also comply with data storage and access requirements of the Utrecht University.

### Ethical approvals and consent to participate

We obtained ethical clearance for all the phases of the study from the University of the Witwatersrand Human Research Ethics Committee (clearance certificate number: M190641). Departmental approval was granted by the Johannesburg Health District (DRC Ref: 2019-10-005 and National Health Research Database reference number: GP_201910_031). Written consent for interviews will be obtained from all participants. All participants will be provided with written information about the research, and they will also be verbally informed that their participation is voluntary and that they may withdraw from participation at any time (see S3 Appendix Participant Information sheet).

There are no risks or direct benefits for participating in the study. Participants may benefit by taking part in the study because many people find that it is useful to discuss their experiences, opinions and provide feedback. We believe that the information from this study will help the South African Department of Health better understand and strengthen the ART services provided to patients at large. All participants will be informed of these benefits.

All information discussed during the interview will be kept strictly confidential; at no point will participants’ personal details be disclosed. The consent forms will be kept separately from all other research documents. Only the study team will have access to the information provided by the participants. All dissemination outputs will present de-identified and, where possible, aggregated data.

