## Introduction

Inconsistent adherence to treatment is a contributing factor to poor health outcomes of people affected by numerous health conditions, including HIV, tuberculosis, diabetes mellitus (DM) and hypertension [1–3]. The World Health Organization (WHO) defines adherence as the degree to which a patient is able to follow a treatment schedule and take medication at recommended times [4–6]. In the context of HIV, lapses in adherence to medication can lead to the development of viral rebound, which can result in immunosuppression and viral resistance [4,7–9].

WHO recommends the use of the HIV drug dolutegravir (DTG) as the preferred first-line and second-line ART treatment regimens for all populations due to its formidable resistance barrier and improved tolerability [10–12]. Despite the advantages of this first-line regimen, in South Africa between 20%-30% of patients with HIV experience clinical, immunological or virological failure from first-line ART due to lapses in adherence [13–15]. This is a concern because of the clinical and cost implications attached to treatment failure [16,17].

Adherence to ART is a complex process that is affected by multiple factors, and numerous studies have attempted to establish what the barriers and facilitators of ART adherence are [18–20]. Individual-level factors such as age, sex, ethnicity, HIV status disclosure and forgetfulness, have been reported as important in predicting ART adherence [21]. However, using individual-level factors one is only able to report a limited proportion of the variability in non-adherence [22]. Good interpersonal relationships between patients and care givers or treatment supporters including healthcare providers, an intimate partner, family members, and friends have been reported as predictors for good adherence [22,23]. In contrast to intrapersonal and interpersonal factors, the community level factors such as poverty, HIV related stigma and discrimination against patients on ART introduce barriers to ART adherence [24]. Additional to community level factors, awareness of healthcare policy level factors like HIV treatment guidelines, policies, and best practices are imperative in ensuring good adherence and maintenance of the continuum of care [25].

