#### Sampling/Sample size

In this study, purposive sampling of patients currently taking ART will be employed to ensure maximum variation among the study sample. We will ensure a diverse sample by considering viral load status (suppressed and unsuppressed time on ART, age (18 years and older), sex (both males and females) and education. Sample size will depend on when saturation is reached; we anticipate that a maximum of 60 IDIs will be conducted across both study settings and viral load status groups (suppressed and unsuppressed). An anticipated number of study participants to recruit is 15 per viral load status group in each study setting (making a total of 30 participants in each study setting).

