#### Data collection

Patients for this phase will be contacted using the contact information that they provided for their facility records or databases used in phase I and II. IDIs will be conducted following a semi-structured interview guide. The guide will comprise open-ended questions covering treatment history, current use of ART and multilevel factors derived from the socio-ecological framework. This will include individual level factors including treatment-related factors (ART regimen, use of non-ART medication), financial and economic factors risk behaviours (substance use), psychosocial factors (cultural beliefs, spirituality), interpersonal-level factors (relationship between patients and treatment supporters or caregivers, such as intimate partners, family members, friends and health care workers), community level factors (social norms regarding HIV and ART, HIV-related stigma and discrimination, HIV-status disclosure), health-system factors (access to HIV and ART services including adherence counselling), and policy level factors (HIV testing and treatment guidelines and policies). Additional probes will be included for each question to promote sharing of detailed information regarding their perspectives and experiences, and to ensure clarification if required (see S1 Appendix study codebook and S2 Appendix interview guide). All IDIs will be audio recorded and transcribed verbatim. Transcripts will be translated into English.

*Deductive themes*. Deductive themes may include treatment history, current use of ART, treatment regimen, financial/economic factors, risk behaviors (substance use), psychosocial characteristics cultural beliefs, spirituality and), relationship related factors (treatment support), community level factors (societal norms, stigma, discrimination, disclosure), and policy level factors (awareness of HIV/ART policies and treatment guidelines).

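### The unqualified statement that taking part carries no risk conflicts with the protocol's own contact route and interview topics and should be corrected, with the information sheet checked against it

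*Protocol article*

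**What the plan says.** The section on ethical approvals and consent states: "There are no risks or direct benefits for participating in the study". It goes on to say that participants may find it useful to talk about their experiences, that the health department may learn from the results, and that participants will be told of these benefits. It makes no parallel statement about telling them of risks. It refers to a participant information sheet in the S3 Appendix, which is not shown.

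The Phase III data collection section describes recruitment: "Patients for this phase will be contacted using the contact information that they provided for their facility records", or from the databases used in Phases I and II. The interview guide covers "risk behaviours (substance use), psychosocial factors (cultural beliefs, spirituality" and also "community level factors (social norms regarding HIV and ART, HIV-related stigma and discrimination, HIV-status disclosure". On recording, the section says: "All IDIs will be audio recorded and transcribed verbatim".

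The Introduction says that "poverty, HIV related stigma and discrimination against patients on ART introduce barriers to ART adherence". The conceptual framework lists HIV-related stigma again among the community-level factors.

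On numbers, the Phase III sampling section says "we anticipate that a maximum of 60 IDIs will be conducted across both study settings".

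**The concern.** The sentence does not claim minimal risk or risk no greater than in routine care. It claims none. Two of the procedures it covers carry a foreseeable risk on the protocol's own premises.

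The first is contact. Someone who approaches a patient with details drawn from an HIV treatment record can reveal that patient's status if the approach reaches another person or is overheard. The second is the interview, in which people are asked, on a recording, about stigma, discrimination, disclosure and substance use. Distress is an ordinary possible consequence of such questions.

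What is at stake is the accuracy of the statement on which consent rests and the attention given to the contact step. If risk is recorded as none, nothing in the text prompts anyone to state a precaution there. People who are contacted and then decline matter too, because for them contact is the whole of their exposure.

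**Working it through.** The protocol attaches no figure to its risk statement, so there is nothing to recalculate. The check is a comparison of the sections.

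**1. What the risk sentence covers.** It refers to participation in the study without limit. Phases I and II are secondary analyses of existing data and Phase IV is a literature review. In practice the sentence concerns the Phase III interviewees, who are the people asked for written consent.

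**2. Contact.** The Phase III text gives the source of the contact details: facility records or the Phase I and II databases. The Phase I data collection section confirms that TIER.Net holds contact details and lists them among the variables to be extracted. The article does not say how the approach is made or worded. The data management section and the limitations paragraph both expect data quality problems in the secondary data, so an out-of-date or shared number is a fair possibility. Phase III invites only active patients, which lowers that possibility without removing it.

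**3. Interview content.** Substance use, stigma, discrimination and HIV-status disclosure are all in the guide, and every interview is recorded and transcribed. The limitations paragraph expects social desirability bias in questionnaire answers on disclosure and stigma, so the authors themselves regard these topics as sensitive.

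**4. The protocol's own premise.** Stigma and discrimination are presented as barriers to adherence, not as harms of research. They still establish that being known to take ART can have social consequences in these settings. That is enough to make unintended disclosure a foreseeable risk.

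**5. Protections that are stated, and what each one covers.**

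| Protection | Section | When it acts |
|---|---|---|
| Ethics clearance for all phases | Ethical approvals | Before the study |
| Written consent, voluntary participation, withdrawal | Ethical approvals | After contact |
| Confidentiality of interview content; access limited to the study team | Ethical approvals | After the interview |
| General promise that personal details are never disclosed | Ethical approvals | No time limit, but no procedure |
| Consent forms kept apart; de-identified outputs | Ethical approvals | After collection |
| Passwords and restricted folders, including voice files | Data storage and access | After collection |

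Apart from the ethics clearance and the general promise, every entry acts after the patient has been reached. None names a risk of disclosure at contact or of distress.

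**6. Size.** Two settings × two viral load groups × 15 participants = 60, which agrees with the stated maximum. The number contacted who decline cannot be derived, because the article gives no acceptance rate.

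**Result.** Item 1 states that there is no risk. Items 2 to 4 describe procedures with foreseeable risk. Item 5 shows measures that reduce some of it, but measures that reduce a risk do not make the statement of no risk correct.

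**The case against.** The strongest case on the other side has four parts.

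*Safeguards exist.* A reader might infer from the risk sentence that the study has no safeguards. The documents do not support that. Consent, withdrawal, confidentiality, separate consent forms, restricted storage of voice files and de-identified reporting are all set out, and one promise about personal details has no time limit. This part of the objection stands in full. What is missing is narrower: any mention of disclosure at first contact or of distress.

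*What participants are told has not been seen.* A reader might also infer that participants will be told there is no risk. The article says only that they will be told of the benefits. The risk wording they receive is in S3. This stands too, so the most that can be said is that they may be misinformed if S3 repeats the sentence.

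*An article condenses.* A contact script or an arrangement for distress may sit in the full protocol or the appendices, so its absence from the article is not itself a fault. That is right. The categorical sentence is different, because it is an assertion and not an omission. If S3 lists risks, the article contradicts S3; if it does not, S3 shares the error. The sentence needs correcting in both cases.

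*The benefit wording is consistent.* The text can be read as offering no direct benefit but a possible indirect one. That reading is fair, and no contradiction is claimed here; a label would make it plain.

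**Conclusion.** The risk statement is wrong as written and conflicts with the Phase III procedures in the same article. The conclusion rests on the quoted text and on one modest assumption: that contact through HIV treatment details, and recorded questions on stigma, disclosure and substance use, carry some foreseeable risk of disclosure or distress.

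It affects up to 60 interviewees and an unknown number who are contacted and decline. With an assumed acceptance of 30% to 50%, contacts would number 60/0.5 = 120 to 60/0.3 = 200. Those are assumed counts of people approached, not of people harmed, and the conclusion does not depend on them.

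A reader might go further and infer that undisclosed, unsuppressed patients will refuse more often and weaken the comparison by viral load status. The documents give no evidence on refusal. Sampling is purposive by viral load status and runs to saturation, so refusals could be met by further recruitment. No estimate, test or sample size is affected. The gain from correcting the sentence is in informed consent and participant safety.

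**What to change.** 1. In the section on ethical approvals and consent, replace the risk sentence with one stating that the foreseeable risks are unintended disclosure of HIV status and emotional distress, and that no direct benefit is expected. Keep the possible value of talking and the gain to services, labelled as indirect benefits.
2. Compare the S3 information sheet with the new wording and align it if it differs.
3. In the Phase III data collection section, add that first contact does not mention HIV until the patient's identity and privacy are confirmed. If the full protocol already contains such a procedure or an arrangement for distress, a cross-reference is enough.

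The cost is a wording amendment with ethics notification and slightly slower recruitment. The interview guide, target numbers and analysis stay as they are.

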## Discussion

The overarching aim of this study is to contribute to knowledge that can provide guidance regarding the barriers and facilitators to adherence for first-line and second-line ART patients and different adherence strategies utilized. Using an integrated multilevel socio-ecological framework, this study will focus on determining the influence of the multiple factors that impact on adherence to ART. In line with socio-ecological frameworks [64,65] and propositions, the findings from this study will be discussed under four units of analysis: intrapersonal level, interpersonal level, community level and policy level factors.

### Intrapersonal factors

The client knowledge, attitudes, experiences and perceptions coupled with analysis of the intrapersonal factors influencing adherence to ART play a fundamental role in maintaining adherence [35]. Intrapersonal level factors such as being age, sex, substance abuse, and comorbidities will be discussed, in line with the existing literature [66–69].

### Interpersonal level factors

The trust and communication between patients on ART and treatment supporters is essential in improving and maintaining optimal adherence to treatment [25]. Some studies have reported treatment support as a predictor of adherence [38,70]. In this study, the interpersonal level factors consisting of relationships between patients and family members, friends, intimate partner(s) and healthcare providers will be discussed against previous studies to provide guidance on the role of treatment supporters in strengthening treatment adherence.

### Community level factors

The findings concerning community level factors will consider the importance of patients understanding of social norms, cultural barriers and reduction of poverty, stigma and discrimination against people living with HIV and on ART [71]. Information on poverty, culture, HIV related stigma, and discrimination caused by misconceptions will be discussed in line with existing literature to provide a critical assessment on the role of community level factors on ART adherence.

### Policy level factors

The policy-level factors address awareness and influence of public health policies, guidelines, and standards on patients [72,73]. The South African HIV programme has undergone several changes since its implementation in 2004 [74]. This study will evaluate patient understanding/awareness of ART adherence or HIV treatment related health policies, guidelines, and best practices that are followed by health providers when providing health services. Knowledge of ART medicines or regimens (names of ART drugs), definitions, and clinical functions of viral load (knowledge of threshold for virological failure and suppression) and CD4 cell count (understanding of high or low CD4 cell count) will be discussed as themes in assessing individual’s awareness of existing HIV treatment policies and guidelines. Additionally, we will be able to provide recommendations on required changes at the policy level to improve treatment adherence.

#### Strengths and limitations

To our knowledge this will be the first study using a social-ecological perspective and a convergent parallel mixed method design to report on combination ART in South Africa. Combining quantitative and qualitative data from public health settings, a controlled environment, the patient perspective and evidence from the region will enable us to make recommendations for a comprehensive, acceptable, and appropriate adherence strategy for the country.

The study presents a fewlimitations. The study will be conducted in a total of eight health facilities (seven of over 120 health facilities in one South African metropolitan municipality (urban setting) and one facility in a rural setting). Therefore, findings may not be generalizable to other municipalities and districts in South Africa, or to other country settings. Furthermore, although there are efforts to ensure good quality of data by the South African Department of Health, supporting partners and research staff, secondary data are subject to quality issues, due to data inconsistencies and missing data. Other potential predictors of adherence, such as disclosure, stigma, and self-reported adherence, will be assessed through a standard questionnaire. This may lead to reporting bias (memory and social desirability biases). Policy-level factors might not probe for relevant factors due to how this study is designed (with it focus on the individual’s awareness of health policies and guidelines which is insufficient to fully assess policy-level factors).

In conclusion, our study will demonstrate how an existing socio-ecological conceptual framework can be used as a tool to provide guidance regarding facilitators and barriers to ART adherence. By populating this framework through secondary data analysis, participant interviews of PLHIV who are taking ART and a systematic review comparing adherence intervention strategies for the chronic conditions, this mixed method study will provide evidence on factors affecting treatment adherence at different socio-ecological levels and guide context-specific intervention strategies to improve ART adherence. We believe that the use of our study results to strengthen adherence intervention will subsequently improve health outcomes and decrease the number of patients switching to complex treatment such as second-line and third-line regimens.

### Dissemination

Findings from this research will be submitted for doctoral degree purposes (by thesis). Peer reviewed publications and scientific conference presentations will be developed. Results of the research will be shared with the research participants, donors, and health facilities.
